### Data analysis plan

All variables will be summarized by absolute and relative frequencies or means and medians. Standard deviations, interquartile ranges, and 95 % confidence intervals will also be reported. Possible associations will be evaluated by hypothesis tests and/or generalized linear models and generalized estimating equations to compare the results over time. Inter-rater agreement will be measured by percent agreement and Gwet’s agreement coefficient [28] for the patients’ questionnaires and audits of the medical records. The communication flow among points of care will be measured and analyzed using standard tools from social network analysis. The spatial distribution of the geographical location of patients’ residence will be mapped, and kernel density will be estimated. The data analysis will be performed using R software [36], and we will adopt a significance level of 5 %.

### Study status

At this time, the Internet-based platform has been fully implemented. The DLC was conducted from July 2014 to July 2015. All data related to the health providers have been collected. The Lean Six Sigma project was completed in March 2016. The patients’ selection and inclusion began in November 2014 and was completed in March 2016. Patient follow-up visits are underway. The telemedicine consultations began in April 2016.

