### Interventions

The strategy comprises an Internet-based platform developed as a social network tailored to health professionals’ use that allows the sharing of patients’ information, documents, and treatment plans between the hospital and 18 PCUs. In addition, telemedicine support will be made available for patients who, for any reason, do not receive specialist services. An electronic knowledge platform will also be developed to keep the health professionals updated through a distance-learning course (DLC) in clinical management focused on diseases that are part of the Brazilian ACSC list.Communication platformsAn Internet-based social network that was developed using free software (based on the open source project Hubzilla [17], formerly known as Redmatrix) and was tailored for this intervention will be made available to the HMMD and PCU health teams [18]. This platform will host private communications among the health providers about their common patients. This shared information will flow through secure channels using the HTTP Secure (HTTPS) protocol to ensure that patients’ information can only be accessed by the appropriate health professionals, whose identity will be authenticated by their credentials (login and password).The platform’s interface includes a hospitalization alert that will ask for specific information that can help the hospital teams to manage the patient during their stay. The responses from the PCU will be incorporated into the hospital electronic medical record. Afterwards, the discharge summary and prescriptions will be delivered to the PCU through a similar discharge alert. Beyond the sharing of information, each alert allows for an online asynchronous conversation to develop between the professionals at each end.Additionally, a telemedicine service (already implemented at HMMD) will be made available to those patients followed during the study, who, for any reason, do not reach specialized services in the SUS. For example, long waiting times for consultations or more sophisticated exams, patient’s lack of resources to pay for transportation to the point of care, or simply absenteeism are situations that can hinder treatment plans, potentially harming patients’ clinical outcomes. Eligible patients will be referred by the primary care teams. These patients will then visit HMMD, where they will be seen by an HIAE physician or nurse specialist via telemedicine equipment. This is an ongoing project supported by the HIAE and the Ministry of Health, with benefits reported among patients seen in the HMMD emergency room [19].Clinical management updating DLCA DLC based on the Brazilian ACSC criteria, focusing on physicians, nurses, and multi-professional staff, will be implemented. The DLC will be hosted by the HIAE Teaching Department’s structured platform, Taleo™. This knowledge platform was conceived to transmit and record web conferences, host discussion forums, and store and transfer archives. Other educational resources, such as structured clinical cases, will be developed to illustrate situations faced by health providers in real-world scenarios.The DLC will be divided into five modules, each 8 weeks in duration, covering the Brazilian ACSC list: respiratory, cardiovascular, diabetes, gastroenterology and mixed infectious diseases, and major health risk factors (smoking, alcoholism, drugs, pain, nutrition, and physical inactivity). Web conferences will be transmitted and recorded on a weekly basis. The 18 PCUs and HMMD will participate in the web conferences, which will feature a presentation on an ACSC by a professional expert speaker and a professional generalist’s comments on specific issues to provide participants with updated evidence-based knowledge. A tutor will encourage discussions in the forum, using a structured clinical case as a tool to demonstrate the applicability of the scientific evidence. The use of the ACSC-related guidelines and/or of evidence-based protocols will be emphasized. After each module, a face-to-face meeting will be carried out to emphasize teamwork and clinical decision-making processes, wrapping up the module content with mixed discussion groups tasked with generating proposals from the health providers for applying evidence-based recommendations at their care facilities. The DLC participants will be evaluated based on their participation in the discussion forums, weekly quizzes, and a final exam at the end of each module. Additionally, the participants will use a structured questionnaire to evaluate each module in terms of their satisfaction with the DLC structure, content, relevance to clinical practice, and feasibility of application in the workplace [see Additional file 1].

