
### Sample and study design for impact evaluation

PatientsThe impact evaluation of the integration strategy will use a quasi-experimental cohort with historical controls design. Participants will be adult patients hospitalized for ACSC who will be followed up 1 year after their hospital discharge. Patients’ data will be compared with data on the same patients from different time periods as historical controls, using medical records dating at least 1 year before and 1 year after the patients’ inclusion in the study.The sample of patients will be selected in two stages. First, a convenience sample of 18 PCUs will be selected, as described above. In the second stage, 560 hospitalized adult patients living in the territories covered by and registered in the selected PCUs will be selected based upon their main or secondary diagnosis, which must fit the Brazilian ACSC criteria, excluding female pelvic disorders and pregnancy-related diseases (Table 2). The calculation of this sample size was based on the 2013–2014 HMMD incidence of 30-day readmissions for ACSC, which was 16 %. This sample size will permit a valid logistic model with up to nine covariates to be fit [20].

**Table 2 Tab2:** Diagnoses included in this study and their International Classification of Diseases (ICD-10) codes

Diagnosis	ICD-10 code
Infectious gastroenteritis and complications	E86, A00–A09
Gastrointestinal ulcer	K25–K28, K92.0, K92.1, K92.2
Ear, nose, and throat infections	H66, J00–J03, J06, J31
Bacterial pneumonias	J13–J14, J15.3–J15.4, J15.8–J15.9, J18.1
Diseases of the lower airways	J20, J21, J40–J44, J47
Asthma	J45–J46
Tuberculosis	A15.4–A15.9, A16.3–A16.9, A17.1–A17.9
Pulmonary tuberculosis	A15.0–A15.3, A16.0–A16.2
Heart failure	I50, J81
Hypertension	I10–I11
Angina pectoris	I20, I24
Cerebrovascular diseases	I63–I67, I69, G45–G46
Diabetes mellitus	E10–E14
Infection in the kidney and urinary tract	N10–N12, N30, N34, N39.0
Epilepsies	G40–G41
Syphilis	A51–A53

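### In the Objective 4 same-patient comparison, no patient's 12-month pre-inclusion control year lies wholly before the distance-learning course, so the contrast cannot be read as the course effect

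*Protocol article*

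**What the plan says.** Under Sample and study design for impact evaluation, the control is defined within patient: "Patients’ data will be compared with data on the same patients from different time periods as historical controls". The length of the comparison window is set in the same sentence, where the data are to be obtained "using medical records dating at least 1 year before and 1 year after" each person's entry. The same section later repeats this window around the hospitalization and ties it to the historical control design. The dividing line is thus each patient's own entry into the study, not the start of an intervention.

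Study status gives the dates. On the course it states: "The DLC was conducted from July 2014 to July 2015". On recruitment it states: "The patients’ selection and inclusion began in November 2014 and was completed in March 2016". For the platform it says only "At this time, the Internet-based platform has been fully implemented", with no start date. Telemedicine consultations began in April 2016.

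Table 1 states that Objective 4 is to assess the longer-term impact of both strategies, communication and course, through the patient cohort. Its data-analysis row places the modelling of readmission, including comparison over time, under Objective 4. Objective 3 covers all adult admissions with an ambulatory care sensitive condition from 2013 to 2017 and names 30-day readmission among its outcomes, but the models listed for it are for length of stay and mortality.

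**The concern.** A before/after comparison needs a before period free of the intervention. The course was directed at the hospital and primary care teams, so a patient can be exposed to its effect through those teams well before the index admission. A control year anchored to inclusion, when inclusion opens after the course has begun, compares time partly or wholly after course start with later time of the same kind. The other side is affected too: for the earliest patients, some 7 to 9 months of the follow-up year fall while the course was still running.

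At stake is the interpretation of the cohort result. A null pre/post contrast could mean that the course does nothing, or that its effect was already present in the control year. The data as arranged could not separate the two.

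**Working it through.** **The plan's own figure.** The article gives no overlap figure. Its one relevant number is the sample size of 560, built on the "HMMD incidence of 30-day readmissions for ACSC" of 16% and nine covariates. Assuming ten events per covariate (no rule is named), 9 × 10 / 0.16 = 562.5. Conversely, 560 × 0.16 = 89.6 events, or 9.96 per covariate. So 560 is reproduced, and the overlap does not affect it.

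**Inputs for the overlap.** Course July 2014 to July 2015; inclusion November 2014 to March 2016; look-back of at least one year. Days of the month and the accrual pattern are not given, so both are assumed and varied.

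**Without any accrual assumption.** From course start to first inclusion is at least 3 months (31 July to 1 November 2014) and at most 5 (1 July to 30 November 2014). The smallest exposed share of a 12-month control year is therefore 3/12 = 25% to 5/12 = 42%. From July 2015 on, it is 100%.

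**With uniform accrual.** Let t be months from 1 July 2014 to inclusion, uniform on 4 to 21 (1 November 2014 to 31 March 2016).

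- Share after course start is min(1, t/12). Its mean is [(12² − 4²)/24 + 9]/17 = (5.33 + 9)/17 = 84.3% (84.4% counted by day).
- Fully post-start control year: (21 − 12)/17 = 52.9%.
- Share while the course was running, taking its end as 1 July 2015: t/12 up to 12 months, then (24 − t)/12. Mean (5.33 + 5.63)/17 = 64.5%.
- Share after course end: (9²/24)/17 = 19.9%.
- Two-year look-back, share after course start: mean of t/24 = 12.5/24 = 52.1%.

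**Sensitivity**, moving the day of the month for each date and then the accrual pattern:

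| Quantity | Result |
|---|---|
| After course start, 12-month look-back, uniform accrual | 80–86% |
| Same, accrual linearly front- or back-loaded | about 68–77% or 93–96% |
| While course running, 12-month look-back, any of these patterns | 60–73% |
| Inclusion days with a fully post-start control year | about 47–53% |
| After course start, two-year look-back, uniform accrual | 48–52% |

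**Illustration on assumed numbers.** Suppose the course lowered readmission from 16% to 12%, acted in full from its first day, and the follow-up year were fully exposed. With 84% of control time exposed, the visible contrast would be 4 × (1 − 0.84) = 0.6 points. With a two-year look-back (52%) it would be 4 × (1 − 0.52) = 1.9 points. Gradual exposure makes the real dilution smaller: according to the Interventions section, "The DLC will be divided into five modules, each 8 weeks in duration", so delivery alone took 5 × 8 = 40 weeks.

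**The case against.** The best defence has four parts, and much of it stands.

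- **The course is only one component.** Platform exposure is triggered by a hospitalization (admission alert, reply, discharge summary), so splitting at the index admission is reasonable for it. Telemedicine started after the last inclusion and touches no control year. A reader might infer that the control year is exposed to the whole intervention. The documents do not support that: the overlap is shown for the course only.
- **Unexposed data exist.** Objective 3 holds 2013–2017 admissions, about 18 months of them before the course. It would be wrong to say that the study has no unexposed comparator. Even so, the listed readmission models sit under Objective 4.
- **No single share can be stated as fact.** A figure of 84% needs uniform accrual, a 1 July start, exactly 12 months of look-back and full exposure from day one. The article allows a longer look-back, the modules came in sequence, and participation was voluntary.
- **Net bias toward zero is not established.** Contamination alone dilutes a benefit. But patients enter through a hospitalization, so regression to the mean or disease progression can act either way, and the record-quality project completed in March 2016 may change what is recorded.

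A reader might also infer that the 16% baseline is spoiled. If it covers two full calendar years, 6 of 24 months follow course start, but that figure only sizes the model, and 560 is unaffected.

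The Discussion concedes limits in isolating effects but does not mention this overlap. An unshown analysis plan may define periods more finely, yet the control definition and the conflicting dates both stand in this article.

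**Conclusion.** The point holds for the course component of the Objective 4 same-patient comparison. That no 12-month control year is wholly pre-course follows from the stated dates alone. The average size depends on assumptions: about 80–86% of control time after course start under uniform accrual, 68–96% under the other patterns tried, and about half with a two-year look-back. These are shares of time since course start, not measures of full exposure. The contamination part dilutes any benefit of the course; the net direction of bias in the contrast is unknown. Platform overlap cannot be assessed without a go-live date. The sample size and the Objective 3 data are not put in doubt.

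**What to change.** 1. Define exposure by calendar date: pre-course is before July 2014; roll-out is July 2014 to the later of course end and platform go-live; exposed is thereafter. State the go-live date.
2. Make the primary before/after comparison of 30-day readmission on the Objective 3 admissions (2013–2017), with January 2013 to June 2014 as the unexposed period, and list a readmission model there. A 30-day readmission needs an index admission in the control period, which the admissions file supplies by construction and a cohort patient's prior year may not.
3. In the 560-patient cohort, enter calendar exposure period as a time-varying term in the generalized estimating equations, using the longer look-back that the protocol already permits. Two years gives even a patient included on 31 March 2016 about 3 pre-course months (1 July 2014 is 21 of 24 months back).
4. State that the pre-/post-inclusion contrast will not be interpreted as the course effect.

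The cost is analysis wording plus further-back abstraction from paper records. The unexposed baseline becomes 18 months rather than the 24 of 2013–2014. Earlier control time also means longer and unequal gaps before inclusion, and so more ageing and disease progression. Imposing one fixed year, July 2013 to June 2014, on all 560 is not advised for that reason: the gap to inclusion would run from about 4 to 21 months.

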## Discussion

There are multiple potential difficulties in adopting an innovation that involves changes in working processes in the health services. According to implementation science models, certain institutional and personal attributes enhance culture, environment, and teamwork, as well as the reaction of these things to inner and outer pressures [37–39]. In general, these innovations demand behavior change among health teams in management and assistance tasks. Adding a new task in addition to the existing ones is a matter of concern in health services in terms of work overload and prioritization of actions concerning relevance to patient care. The incorporation of evidence-based practices tends to compete with previously established processes already being used by health providers, thus also requiring organizational adaptations [40]. Creativity and the rational use of available technology can be useful in tackling fragmentation of care, improving patient outcomes, and lowering health-related costs, all of which are urgent needs.

In the Brazilian health system, the biggest universal system in the world in terms of population and territorial coverage, an efficient RHAN is a necessity that is being built. Nevertheless, it is a difficult task to accomplish. The social network platform described in this protocol will be incorporated through the development of work processes and flows involving the HMMD and PCU teams. This project will gather information about obstacles and critical situations that affect them. The DLC seeks to introduce an educational tool into health workers’ routine that is necessarily easy to access, useful, and feasible, and through which relevant information can be reached and applied in clinical practice. The DLC will be tested and improved based on input from the health provider volunteer participants, who will evaluate certain aspects of the DLC related to access, content, and educational resources. The health professionals’ profiles related to burnout, quality of life, mindfulness, and sociodemographic and educational characteristics will contribute information about how the organization of the SUS affects their work possibilities and, ultimately, their overall health. This study also aims to shed light on feasible options for testing the effectiveness of communication and capacity building strategies for health providers, as well as tools designed to improve these capabilities, provide recognition, and empower the health providers.

The study design is mainly focused on the implementation processes of the interventions to be tested among health professionals, including assessments of the effects of obstacles, resistances, new skills, and new process developments on health teams’ communication and on the availability of evidence-based scientific knowledge. The originality of this study is found in its assessment of a DLC administered to health professionals providing care to a shared group of patients over different points of care and in the implementation of an Internet-based communication platform as a social network. The hospitalized patient-selection process will allow the study to include members of the population who are socially and environmentally vulnerable. The major strength of this study is its status as a pragmatic intervention conducted in a real-world setting. However, there will be methodological limitations in terms of isolating the effects of the proposed interventions. A comprehensive strategy to implement RHAN must consider not only technological innovation and its results, but all features that can interfere with the necessary steps to achieve consolidated changes in work processes and patients’ outcomes. Data quality, safe information channels, and a healthy workforce are themes that are investigated in this research project.

## Abbreviations

ACSC, ambulatory care sensitive condition; CEJAM, Center of Studies and Research [name] (Centro de Estudos e Pesquisas, [name]); CONEP, National Research Ethical Commission (Comissão Nacional de Ética em Pesquisa) ; DLC, distance-learning course; FAPESP, São Paulo State Research Agency (Fundação de Amparo à Pesquisa do Estado de São Paulo); HIAE, Hospital Israelita Albert Einstein; HMMD, Hospital Municipal [name] - M’Boi Mirim; PCU, primary care units; PPSUS, Research Program for the SUS (Programas de Pesquisa para o SUS); RHAN, Regional Healthcare Attention Network; SIGA SAÚDE, Municipal Integrated System for Health Assistance Management  (Sistema Integrado de Gestão da Assistência à Saúde) ; SUS, Brazilian Unified Health System (Sistema Único de Saúde)
